## Abstract

**Background:**

Mobility limitation—the loss of exercise capacity or independent living ability—is a common geriatric syndrome in older adults. As a potentially reversible precursor to disability, mobility limitation is influenced by various factors. Moreover, its complex physiological mechanism hinders good therapeutic outcomes with a single-factor intervention. Most hospitals have not incorporated the diagnosis and evaluation of mobility limitation into medical routines nor developed a multidisciplinary team (MDT) treatment plan. We aim to conduct a clinical trial titled “A Multidisciplinary-team approach for management of Mobility Limitation in Elderly (M-MobiLE)” to explore the effect of the MDT decision-making intervention for mobility limitation.

**Methods:**

The M-MobiLE study will be a multicenter, randomized, and controlled trial. We will recruit a minimum of 66 older inpatients with mobility limitation from at least five hospitals. Older patients with mobility limitation admitted to the geriatrics department will be included. Short-Physical Performance Battery (SPPB), Activities of Daily Living (ADL), Function Impairment Screening Tool (FIST), Geriatric Depression Scale (GDS-15), Short Form − 12 (SF-12), Fried frailty phenotype, social frailty, Morse Fall Risk Scale, SARC-CalF, Mini-Mental State Examination (MMSE), Mini-Nutritional Assessment Short-Form (MNA-SF), and intrinsic capacity will be assessed. The intervention group will receive an exercise-centered individualized MDT treatment, including exercise, educational, nutritional, medical, and comorbidity interventions; the control group will receive standard medical treatment. The primary outcome is the change in the SPPB score, and the secondary outcomes include increased SF-12, ADL, FIST, MMSE, MNA-SF, and intrinsic capacity scores and decreased GDS-15 and SARC-CalF scores.

**Conclusion:**

Our results will help develop a multidisciplinary decision-making clinical pathway for inpatients with mobility limitation, which can be used to identify patients with mobility limitation more effectively, improve mobility, and reduce the risk of falls, frailty, and death in older inpatients. The implementation of this MDT strategy may standardize the treatment of mobility limitation, reduce adverse prognosis, and improve quality of life.

**Trial registration:**

ChiCTR, ChiCTR2200056756, Registered 19 February 2022.

## Introduction

The proportion of older adults is increasing in society. Safeguarding healthy aging in older adults has significant implications for individuals and society. Mobility limitation—a type of geriatric syndrome —refers to the loss of exercise capacity or independent living ability [1]. It is often the first noticeable sign of functional decline [2, 3] and is diagnosed by assessing a person’s ability to move from a bed or chair, walk a quarter of a mile, or climb stairs independently, or by assessing distance walked from the home [1, 3–6]. Studies have shown that approximately one-third of geriatric patients experience mobility limitation [7]. Notably, hospitalized patients are particularly affected, with the incidence of loss of movement being as high as 17% due to the limitation of movement space and the presence of diseases [8]. Additionally, weekly bed rest may result in losing 5–10% of muscle strength in older adults during hospitalization [9, 10].

The effect of mobility limitation on older adults is multi-dimensional. Mobility limitation was significantly associated with depressive symptoms [11], decreased quality of life [12], increased disability [13], falls [14], and mortality [15]. Signs of mobility limitation can be used as indicators to predict physical health impairment, loss of independent living ability, hospitalization, and death. Additionally, mobility limitation is a huge hidden danger affecting the health and safety of older adults. It is affected by different factors, including nutrition [16, 17], psychology [11], obesity [18, 19], sedentary lifestyle [14, 20], muscle dysfunction, joint damage [21, 22], and cardiovascular [23, 24], respiratory [24, 25], and endocrine diseases [26–28].

Mobility limitation has received widespread attention due to increased awareness of healthy aging. Some studies have achieved remarkable results with the intervention of single factor, such as testosterone [26, 29], protein [17], blood pressure [30], and resistance exercise [31, 32]. Therefore, the feasibility and necessity of mobility limitation intervention have been clarified.

However, since mobility limitation indicates a decline in the body’s comprehensive reserve capacity [3], many influencing factors co-exist; it is difficult to use a single indicator for its intervention. Additionally, treatment with a single factor cannot remove the root cause in all patients. Mobility limitation is often accompanied by comorbidities or functional decline; therefore, older adults’ physical, psychological, and social functions should be evaluated from multiple dimensions. It is crucial to comprehensively assess the influencing factors of mobility limitation and administer individualized multidisciplinary team (MDT) treatment. However, the diagnosis and treatment of mobility limitation are not currently integrated into routine medical care, and there are no studies on using the MDT approach for treating mobility limitation in a hospital setting [1, 14].

This study aims to conduct a clinical trial called " A Multidisciplinary-team approach for management of Mobility Limitation in Elderly (M-MobiLE)” in a hospital setting to determine the effect of MDT in managing mobility limitation. We hypothesize that MDT can improve mobility (Short-Physical Performance Battery [SPPB]) in older adults with mobility limitation. Additionally, we hypothesize that MDT can improve intrinsic capacity, quality of life, depression, cognition, frailty, and nutritional status, reduce the incidence of frailty, falls, and other adverse events, shorten hospital stay, and reduce mortality.

## Method and design

### Study design and setting

We will conduct a prospective, multicenter, randomized, parallel, and controlled trial in the geriatric departments of at least five hospitals. A two-arm follow-up cohort will be established in this study. The control group will be placed on routine treatments, and the intervention group will be treated with an MDT approach, including exercise, educational, nutritional, medical, comorbidity, and environmental interventions. The multidisciplinary consultation team will include geriatricians, rehabilitation physicians, nutritionists, nurses, pharmacists, ophthalmologists, otolaryngologists, neurologists, cardiologist, rheumatologists, endocrinologists, psychologists, and pain management physicians. Furthermore, we will develop an individualized exercise prescription based on the “International Exercise Recommendations in Adults (ICFSR): Expert consensus guidelines” and the recommendations of the rehabilitation physician. The assessment for mobility limitation will be completed within 48h after admission, followed by MDT. Guidance recommendations for comprehensive interventions will be extended to 2 years after discharge, and follow-up assessments will be performed at 3, 6, 12, and 24 months after discharge (Fig. 1).

**Fig. 1 Fig1:**
[figure not shown]
Flow chart of the M-MobiLE study. SPPB, Short-Physical Performance Battery; MDT, multidisciplinary team; ADL, Activities of Daily Living; GDS-15, Geriatric Depression Scale; MMSE, Mini-Mental State Examination; MNA-SF, Mini Nutritional Assessment short-form; IC, Intrinsic Capacity

#### Inclusion criteria

Mobility limitation will be screened by asking the patient to answer subjective questions or through a simple physical fitness test [1, 3, 33, 34]. We have integrated both methods to ensure the accuracy. The following conditions will be used for screening: (1) compared with the past, it is now more difficult to climb 10 steps in a row or walk 400 m (including changes in style or speed reduction), (2) five time-chair sit-to-stand ≥ 14 s, and (3) timed Up and Go ≥ 10 s.

Inpatients who meet the following criteria will be included in the study: (1) age ≥ 60 years, (2) meet the criteria for mobility limitation, (3) hospital stay ≥ 6 days, (4) SPPB ranges from 4 to 9 (Mobility limitation is defined as SPPB≤9 points [33, 35]. However, in order to ensure the safety of exercise in the hospital, we will exclude patients with a score of 4 or less.), and (5) conscious and able to communicate with the researcher.

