### Measurements

#### Assessment

The initial assessment will be completed within 48 h of admission. Subsequently, follow-up by telephone will be performed at 3, 6, and 24 months after discharge. Additionally, a face-to-face follow-up will be conducted at 12 months after discharge (Fig. 2). SPPB will be used to assess mobility. SPPB is a well-established tool for assessing lower extremity physical performance status. It includes balance, pace, and standing-sitting tests, with a total score of 0–12, with lower scores indicating poorer exercise capacity [38]. The activities of daily living (ADL) and the functional impairment screening tool (FIST) scales will be used to assess physical function. The FIST assessment entails 16 questions with a total score of 16. The higher the score, the better the performance [39]. We will use Geriatric Depression Scale (GDS) -15 to assess depression. It has a total score of 15 points, with 5–9 indicating that the patient may be prone to depression and ≥ 10 indicating depression [40, 41]. The Short Form-12 will be used to assess the quality of life [42]. Fried frailty phenotype includes unintentional weight loss, exhaustion, weakness, slowness, and low physical activity. A score of 0 indicates robustness, 1–2 indicates pre-frail, and ≥ 3 indicates frailty [43]. Moreover, we will evaluate social frailty using the Help, Participation, Loneliness, Financial, and Talk (HALFT) scale, and those who score ≥ 3 will be classified as socially frailty, 1–2 as pre-social frailty, and 0 will be considered normal [44]. Additionally, the Morse Fall Risk Scale will be used to assess falls. Scores ≤ 23, 24–44, and ≥ 45 are classified as low intermediate and high risks, respectively [45].

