**Fig. 4 Fig4:**
[figure not shown]
The M-MobiLE exercise intervention program includes aerobic, resistance, balance, and stretching exercises. An individualized exercise program will be developed for the patient based on SPPB scores

Aerobic exercises will be conducted for 30–60 min daily, and the exercise duration can be gradually increased. Patients will be asked to complete at least 150 min of aerobic exercise per week, at least 5 days a week, at an intensity such that the patient has mild dyspnea when active but can still talk easily. Resistance exercises will be performed progressively, gradually increasing the amount of exercise. Patients will perform muscle-strengthening activities at least two days a week. Balance exercise will be based on the actual situation of older adults to choose a suitable method and prevent injury. Patients can borrow a stable chair for assistance at the beginning of the exercise or exercise accompanied by others. Stretching exercises will be performed at least twice a week. The specific amount of exercise will be determined during the training by a rehabilitation physician to ensure exercise safety. During hospitalization, patients in the intervention group will be trained 3–5 times weekly. After the exercise, patients will record their experienceit in the exercise manual: easy, difficult, or very difficult. Additionally, patients will be instructed to keep recording in their exercise diaries after discharge, filling in the number of completed weekly sessions and training experience until the last follow-up.

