### Sample size

This will be a parallel randomized-controlled study, and the ratio of the intervention to the control group will be 1:1. A randomized-controlled trial (RCT) in 2021 [55] reported an SPPB of 6.1 points in the control group, and the mean difference between both groups after exercise intervention was 2.4 [56]. Our sample estimate is a one-sided test with a first-class error of 0.025 and a power of 90%. The sample size N1 = N2 = 26 was calculated using PASS 15. Assuming that the rate of loss to follow-up is 20%, the minimum sample size will be N1 = N2 = 26/0.8 = 33. Therefore, a minimum of 66 patients will be recruited for this study.

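### Inclusion criterion (4) admits patients with an SPPB of 4, and its own safety note excludes them

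*Protocol article*

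**What the plan says.** Criterion (4) in the Protocol article, Inclusion criteria, consists of a range and a bracketed explanation.

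- The range is "SPPB ranges from 4 to 9".
- The explanation first gives the upper end: "Mobility limitation is defined as SPPB≤9 points".
- It then gives the lower end and the reason for it: "in order to ensure the safety of exercise in the hospital", "we will exclude patients with a score of 4 or less".

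Under Assessment, the SPPB is described as a scale "with a total score of 0–12, with lower scores indicating poorer exercise capacity". The Exclusion criteria section lists an MMSE limit, moderate to severe disability, exercise contraindications, end-stage disease and refusal. It gives no SPPB threshold.

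The same scale is used in two more places. The Fig. 4 caption says that "An individualized exercise program will be developed for the patient based on SPPB scores", and Study outcomes names the change in SPPB as the primary outcome.

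**The concern.** The two halves of one criterion give different answers for a patient who scores 4. Three things make this more than a wording slip.

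- **Safety.** The document gives the lower limit as a protection for exercise in hospital. The intervention arm is built around exercise, with training three to five times a week during the stay. Under one reading, patients whom the note bars for safety can enter the trial and be allocated to that arm.
- **Consistency between hospitals.** At least five hospitals will apply the rule, and each could defend either limit from the text. If they diverge, the enrolled population and the floor of the baseline SPPB distribution will differ by site.
- **Handling after randomisation.** The trial is open-label. If a patient scoring 4 is randomised, someone could later call that patient ineligible with the allocation already known. The document does not say that this will happen, but the contradiction leaves room for it.

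**Working it through.** **Step 1. The two statements as sets of scores.** The inputs are the stated range, the note and the 0–12 integer scale, all from the Protocol article (Inclusion criteria and Assessment).

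| Source within criterion (4) | Rule | Eligible scores |
|---|---|---|
| Stated range | 4 to 9, ends included | 4, 5, 6, 7, 8, 9 |
| Note | at most 9, and not 4 or less | 5, 6, 7, 8, 9 |
| Difference | | 4 |

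The stated range cannot be reproduced from its own note. The two sets differ at exactly one score.

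**Step 2. Can the wording be read so that both hold?** There are two ways to try.

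- The range is read as excluding its lower end. The upper end must then still be included, because the note defines mobility limitation as 9 or below. The text signals no such half-open range.
- The note is read as excluding only scores below 4. Its words cover 4 itself, so this changes the text.

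Each route makes the criterion consistent only by altering one of the two statements, and they lead to different limits.

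**Step 3. Does other text decide it?** The mobility-limitation screen in the same section uses a stairs or walking question, a chair-stand time and a Timed Up and Go time, with no lower SPPB limit. The Exclusion criteria contain no SPPB limit either. Moderate to severe disability is excluded but is not tied to an SPPB score. Figs. 1 and 4 are not visible here, so nothing is claimed about what they show.

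**Step 4. How many patients?** The plan's total first: 26 / 0.8 = 32.5, rounded up to 33 per arm, and 2 × 33 = 66, as stated in Sample size. If a share p of patients who would be enrolled under the 4-to-9 range score exactly 4, the number affected is 66 × p. The document gives no p, so every row below is an assumption.

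| Assumed p | 66 × p |
|---|---|
| 1/20 | 3.3 |
| 1/10 | 6.6 |
| 1/6 (even spread over six scores, about 17%) | 11 |
| 1/4 | 16.5 |

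For comparison, the planned allowance for loss to follow-up is 33 − 26 = 7 per arm, or 14 in total. Post-randomisation removals of score-4 patients, if any occurred, would draw on that allowance. The table only shows scale; the finding rests on steps 1 to 3.

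**The case against.** The strongest reply accepts the inconsistency and disputes its weight.

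- **One boundary score, no bias between arms.** Eligibility is settled before allocation, so a hospital that admits score 4 admits it to both arms. The definition of the primary outcome, the sample-size calculation and the randomised comparison are untouched. This is correct, and no between-arm bias is claimed.
- **Other safeguards exist.** Exercise contraindications and moderate to severe disability are excluded separately, a rehabilitation physician sets the amount of exercise, and with 1:1 allocation about half of such patients would go to control. These points limit the potential harm. They do not say whether a patient scoring 4 may enter.
- **The consequences are conditional.** Divergence between hospitals and removal after randomisation may not occur, and sites may work from a fuller protocol or case report form. That is fair, and both effects are stated here only as possibilities. The published criterion would still contradict itself.
- **The count is weak.** The share scoring 4 is unknown, so 11 of 66 carries no evidential weight. This stands.
- **Fig. 4 proves nothing.** The caption gives no lower limit and contradicts neither clause. This also stands; the figure is mentioned only because it should agree with whatever limit is settled.

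None of this removes the contradiction. Condensing a full protocol into an article does not explain it either, because both statements are present side by side in the same sentence.

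**Conclusion.** The concern holds. Criterion (4) is wrong as written: its range and its note give incompatible answers at an SPPB of 4, and the visible text offers no way to choose between them. This conclusion rests on wording alone and needs no assumed figure.

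Its extent is one integer score of the six in the stated range. The number of patients depends on the unknown share scoring 4; 11 of 66 follows only if scores are spread evenly. Differences between sites and exclusions after randomisation are possible consequences, not demonstrated ones. The point still has to be corrected because the document presents this limit as a safety limit and the trial cannot apply it consistently. This review takes no position on which limit is clinically right.

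**What to change.** 1. The sponsor's clinical team decides which lower SPPB limit is intended and rewrites criterion (4) so that the range and the note state the same limit, with an explicit inequality sign at each end.
2. Check that the flow chart in Fig. 1, the SPPB-based programme in Fig. 4 and the trial registration agree with it.
3. Send the corrected criterion to all hospitals at the same time, before enrolment starts or, if it has started, before it continues.
4. If any patient scoring 4 has already been randomised, keep that patient in the allocated arm for the primary analysis and report the number by arm and by hospital. Eligibility should not be revisited once allocation is known.

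The cost is a one-line amendment and a site notice. The sample-size calculation as stated does not use the eligibility limit, so it does not need to be redone for this point.

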#### Exclusion criteria

Patients who meet the following criteria will be excluded: (1) Mini-Mental State Examination (MMSE) < 10 points, (2) moderate to severe disability, (3) exercise contraindications^*^, (4) end-stage diseases, and (5) refusal to participate. Additionally, participants will be considered lost to follow-up if they miss any follow-up or if necessary clinical data cannot be obtained during the follow-up period.

^*^Exercise contraindications [36, 37]: acute uncompensated diabetes or poorly controlled hypoglycemia; dissecting aortic aneurysm; acute myocardial infarction or recent unstable angina; acute or severe heart failure; poorly controlled atrial or ventricular arrhythmias; severe aortic stenosis; endocarditis or acute pericarditis; poorly controlled high blood pressure; poorly controlled postural hypotension; acute thromboembolism; acute or severe respiratory failure; and fracture within the past 1 month.

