### Study outcomes

The core of this study is to explore the effect of MDT on mobility in older adults with mobility limitation. The primary outcome is a change in the SPPB score, and secondary outcomes include changes in ADL, FIST, GDS-15, SARC-CalF, MMSE, MNA-SF, and intrinsic capacity scores.

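### Counting one missed contact as loss to follow-up can class patients with an observed primary SPPB as lost, and the 20% allowance uses that same term

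*Protocol article*

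**What the plan says.** All references are to the protocol article.

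- **Exclusion criteria.** After the list of patients to be excluded, the section adds that "participants will be considered lost to follow-up if they miss any follow-up or if necessary clinical data cannot be obtained during the follow-up period".
- **Study design and setting.** "follow-up assessments will be performed at 3, 6, 12, and 24 months after discharge".
- **Assessment.** "follow-up by telephone will be performed at 3, 6, and 24 months after discharge", and "a face-to-face follow-up will be conducted at 12 months after discharge". The same section describes the SPPB as balance, pace and standing-sitting tests.
- **Study outcomes.** "The primary outcome is a change in the SPPB score"; the text names no time point.
- **Sample size.** "Our sample estimate is a one-sided test with a first-class error of 0.025 and a power of 90"%, with 26 per arm. Then "Assuming that the rate of loss to follow-up is 20"%, and 26/0.8 gives 33 per arm, 66 in total as a minimum.
- **Randomization.** The trial is open-label.

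**The concern.** The rule makes loss a property of the patient over the whole schedule, not of the primary measurement. Someone with a valid SPPB is reclassified by one missed telephone call, even a call made long after the SPPB was taken. The rule stands among the exclusion criteria, and the sample size calculation counts a lost patient as contributing nothing to the 26 needed per arm. Both suggest that lost means not analysed.

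Two things are then at stake.

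- **Validity.** Attending every contact for two years happens after randomisation and is related to health, mood and engagement. Patients know their arm, and the intervention arm receives continuing guidance and keeps an exercise diary until the last follow-up, so attendance can differ by arm. A comparison restricted to full attenders is no longer a comparison of the randomised groups. This does not depend on any assumed miss rate.
- **Precision.** The 20% allowance has to cover a miss at any of four contacts, not only a missing SPPB.

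**Working it through.** **Inputs from the article.** Difference 2.4 points; one-sided alpha 0.025; power 90%; 26 evaluable per arm; 20% loss; four contacts, one of them face-to-face.

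**Inputs not in the article, so assumed.** The SD; the miss rate per contact, *m*; and how misses cluster within patients.

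**1. The plan's own figure.** 26/0.8 = 32.5, rounded up to 33 per arm, 66 in total. This reproduces. The 26 itself cannot be checked because no SD is given. Solving backwards with a two-sample t-test, 26 per arm corresponds to an SD of about 2.57 to 2.62. Over that range, 26 per arm gives power 0.911 to 0.900.

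**2. Miss rate that the 20% tolerates under the rule.**

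- Independent misses: the share attending all four contacts is (1 − *m*)^4. Setting this to 0.8 gives *m* = 1 − 0.8^(1/4) = 0.054, or 5.4% per contact.
- Fully nested misses (the same patients miss every contact): loss equals *m*, so the 20% holds up to *m* = 20%.

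**3. Consequences at 33 per arm if lost patients are dropped, misses independent.** Power is from the noncentral t distribution with difference 2.4 and *n* = 33(1 − *m*)^4 per arm, over the SD range above.

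| Assumed *m* | Lost, 1 − (1 − *m*)^4 | Left per arm | Power |
|---|---|---|---|
| 5% | 18.5% | 26.9 | 0.91–0.92 |
| 10% | 34.4% | 21.7 | 0.84–0.85 |
| 15% | 47.8% | 17.2 | 0.74–0.76 |

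**4. Partial clustering.** With a beta-binomial model and within-patient correlation 0.3, *m* = 10% gives 24% lost and power about 0.89–0.90; *m* = 15% gives 35% lost and about 0.84–0.85. With correlation 0.5, *m* = 10% gives 19% lost, inside the allowance; *m* = 15% gives 28% lost and power about 0.87–0.88.

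**5. If loss meant only a missing SPPB at one visit.** *n* = 33(1 − *m*). At *m* = 10%, 29.7 per arm and power about 0.94. At 15%, 28.1 per arm and about 0.92–0.93. At 20%, 26.4 per arm and at least 0.90. The 33 per arm then does what the sample size section intends.

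**6. How much observed primary data the rule can remove.** Under independence, the share with an SPPB at one visit who miss at least one of the other three contacts is (1 − *m*)[1 − (1 − *m*)^3]. At *m* = 10% this is 0.9 × (1 − 0.729) = 0.244, about 8 of 33 per arm. Under full nesting it is zero.

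**The case against.** Four points can be made for the plan.

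- **Removal is not stated.** The sentence gives a label. The statistical analysis section names no analysis set and no restriction to completers, and such matters are commonly left to an analysis plan, which is not shown. Dividing by 0.8 is ordinary inflation. A reader might infer that the plan discards these patients, but the article does not say so. This stands, and the point is therefore conditional. It does not dispose of it: the definition is fixed here, among the exclusion criteria, and an analysis plan that kept these patients would have to override what that placement implies.
- **The primary time point is inferred.** No time point is named and the schedule figure is not shown. Month 12 is a reasonable inference because it is the only face-to-face follow-up and the SPPB is performance-based. The defect exists whichever visit is primary.
- **Failure of the 20% is not shown.** A reader might conclude that 20% and 90% power are unlikely to hold. The documents give no miss rate per contact. At 5% the allowance holds, and illness or withdrawal tends to persist across visits, which moves the result towards the nested case. The 20% may also have been chosen with this definition in mind, and 66 is a minimum. All of this stands.
- **Death is not mentioned in the rule.** A reader might infer that deaths after an SPPB measurement count as losses. The text leaves that open, and mortality is among the hypothesised effects in the introduction.

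**Conclusion.** The point holds in conditional form. As written, one missed contact out of four makes a randomised patient lost even when the primary SPPB was obtained, and the 20% allowance uses the same term and treats lost patients as non-evaluable. If the rule governs the analysis, as its placement implies, observed primary data are dropped and the open-label comparison depends on attendance after randomisation.

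The size depends on assumptions that the documents do not settle. The tolerable miss rate per contact runs from about 5.4% with independent misses to 20% with full nesting. The power figures of about 84–85% and 74–76% belong to assumed independent miss rates of 10% and 15% and an SD back-solved from 26 per arm. They show how sensitive the plan is to the definition; they are not a forecast, and they do not establish that the trial is underpowered.

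**What to change.** 1. Remove the sentence from the exclusion criteria.
2. Define missingness per outcome and per visit, so that a missed contact does not remove data from other visits.
3. Name the primary SPPB time point. Analyse every randomised patient with an observed SPPB at that time point in the arm assigned, with a sensitivity analysis for missing values and deaths reported by arm.
4. State in the sample size section that the 20% means a missing SPPB at that time point.

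The cost is a paragraph of wording and a routine sensitivity analysis, with no added patients or visits. The change should be made before analysis, because in an open-label trial a later change to who counts as lost is open to challenge.

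### The loss-to-follow-up rule does not separate death or physical inability to be assessed from ordinary loss, in a trial that expects its intervention to affect mortality and frailty

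*Protocol article*

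**What the plan says.** The rule stands in the protocol article under Exclusion criteria. A participant counts as lost to follow-up after any missed contact or "if necessary clinical data cannot be obtained during the follow-up period". It makes no distinction by reason.

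The other relevant statements are these:

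- **Study outcomes:** "The primary outcome is a change in the SPPB score". No time point is given there.
- **Assessment:** the SPPB is described "with a total score of 0–12, with lower scores indicating poorer exercise capacity", so the scale has a floor of 0.
- **Study design and setting:** "follow-up assessments will be performed at 3, 6, 12, and 24 months after discharge". Assessment adds that "follow-up by telephone will be performed at 3, 6, and 24 months after discharge", which leaves 12 months as the one face-to-face contact.
- **Introduction:** the intervention is hypothesised to "reduce the incidence of frailty, falls, and other adverse events, shorten hospital stay, and reduce mortality".
- **Sample size:** 26 per arm is divided by 0.8 for 20% loss to follow-up, giving 33 per arm and 66 in total.
- **Statistical analysis:** t-test or Wilcoxon rank-sum test for continuous variables. The article gives no separate rule for deaths.

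**The concern.** A patient who dies during follow-up misses the remaining contacts and can supply no further data, so both limbs of the rule apply. A living patient whose condition prevents any assessment meets the second limb. In both cases the missing SPPB may itself reflect failed mobility or survival, which is different in kind from a patient who moved away or withdrew.

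The protocol expects MDT to change mortality and frailty. By its own hypotheses, then, the chance of having an SPPB value may depend on both outcome and arm. A comparison limited to those alive and assessable is no longer protected by randomisation. If MDT keeps frail patients alive and testable, their low scores enter only the MDT mean and the benefit is understated. If more frail patients drop out on MDT, it is overstated. The trial is also open-label, so the judgement that data could not be obtained is made with knowledge of allocation.

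**Working it through.** **1. The plan's own figure.** 26 / 0.8 = 32.5, rounded up to 33 per arm and 66 in total. This agrees with the article. It also shows that the 26 are the patients left after loss, so lost patients are sized as not contributing.

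**2. Implied SD.** The article states no SD. A two-sample t-test with 26 per arm, one-sided 0.025 (equivalent here to two-sided 0.05) and 90% power needs a standardised difference of 0.917. With the planned 2.4 points, SD = 2.4 / 0.917 = 2.62. Solving on a grid gives 2.57 to 2.61 with the noncentral t and 2.62 to 2.66 with the normal approximation, so about 2.6.

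**3. Illustration A: the lowest scorers are removed.** Assumption: scores are normal and the lowest fraction p of an arm is dropped. The mean of those remaining rises by SD × φ(z_p) / (1 − p).

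- p = 0.20: 2.62 × 0.280 / 0.80 = 0.92
- p = 0.10: 2.62 × 0.1755 / 0.90 = 0.51

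| Removed, control / MDT | Shift in MDT minus control |
|---|---|
| 20% / 10% | 0.51 − 0.92 = −0.41 |
| 10% / 20% | 0.92 − 0.51 = +0.41 |
| equal rates | 0 |

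The shift of 0.41 is 17% of 2.4. If removal is only correlated 0.5 with the underlying score, simulation gives −0.20 for the first row. The removal rates are assumptions; the article gives none.

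**4. Illustration B: absent patients are counted at 0.** Assumption: assessed patients average 6.1 (control figure in Sample size) and 8.5 (6.1 + 2.4), and a fraction p in each arm scores 0. The difference is 8.5(1 − p_MDT) − 6.1(1 − p_control).

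| Absent, control / MDT | Calculation | Difference |
|---|---|---|
| 0% / 0% | 8.50 − 6.10 | 2.40 |
| 20% / 20% | 6.80 − 4.88 | 1.92 |
| 20% / 10% | 7.65 − 4.88 | 2.77 |
| 10% / 20% | 6.80 − 5.49 | 1.31 |
| 20% / 0% | 8.50 − 4.88 | 3.62 |
| 0% / 20% | 6.80 − 6.10 | 0.70 |

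An analysis of assessed patients alone shows 2.40 in every row. Giving deaths a 0 here is a device to show sensitivity, not a proposal.

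**5. Comparing the two.** Both models say the restricted comparison can err in either direction. They differ in size, and they disagree on equal rates: the bias cancels in A, whereas in B the difference falls to 1.92. The result therefore depends on how these patients are represented, which is what the rule leaves unsettled.

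**The case against.** A reader might infer that the protocol removes deaths and disabled patients from the primary analysis. It does not say so. The rule names neither death nor disability, and it defines a status, not an analysis set. Inflating for attrition is ordinary sizing. A statistical analysis plan that is not shown may define who is analysed and how deaths are handled. This stands: removal is implied by the sizing, not stated. What remains is that the article does fix a definition, and read literally that definition covers death.

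The case for physical inability is weaker. A patient who is seen and cannot perform already has a place at the bottom of the 0 to 12 scale, so data can be obtained and the rule need not apply. This also stands, and limits the point to patients who cannot be assessed or whose inability is not scored.

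It is also tempting to say that death or being bedbound would be the usual reason for a missing SPPB. The documents give no support for that. They suggest another reason, since three of the four contacts are by telephone and the SPPB is a performance test. Entry also excludes end-stage disease and moderate to severe disability, which lowers the rates without removing the risk.

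Nor can the 0.41 be read as an estimate of bias. In that model the removed patients average about 2.4 points in controls and 3.9 on MDT, not 0, and a death has no underlying SPPB to truncate.

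Finally, a bias favouring MDT is not the expected case. Under the protocol's own hypothesis of fewer deaths on MDT, both illustrations point to an understated benefit at 20% versus 10%.

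**Conclusion.** The point holds as a defect in a stated definition. The rule merges death and physical inability to be assessed with ordinary loss, while the trial hypothesises effects on mortality and frailty. If it is followed as written, the SPPB comparison is among patients alive and assessable, and absence may depend on outcome and arm.

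The direction and size cannot be fixed from the article. Roughly 0.4 points either way is an illustration that rests on an SD of about 2.6, 20% versus 10% removal, and removal of the lowest scorers; it does not model deaths. The documents do not support a claim that the primary analysis is known to exclude the worst outcomes, or that it is biased in a known direction. This is a worthwhile, inexpensive correction.

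**What to change.** Reword the clause and move it out of the exclusion criteria:

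1. Restrict loss to follow-up to withdrawal or no contact.
2. For a living patient who is reached but cannot attempt SPPB items for physical reasons, score those items 0.
3. Record deaths as deaths, with date. In a supportive comparison, rank them below SPPB 0 and use the Wilcoxon rank-sum test that Statistical analysis already names.
4. Report deaths, unable to perform and true loss separately by arm.

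The cost is protocol and analysis-plan wording and one extra coded field for the reason an SPPB is absent. That field is best filled in prospectively, because the reason may not be recoverable later. The supportive rank analysis gives no difference in points, and the comparison in points still describes survivors, which should be said when it is reported.

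Floor scores also widen the spread. In illustration B with SD 2.6 and 10% at 0 in each arm, the difference is 7.65 − 5.49 = 2.16, the SD rises to 3.32, and power with all 33 per arm is 0.74. That too rests on assumed rates, but it is a reason to settle the rule before data are seen.
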